## INTRODUCTION AND RATIONALE:

Brain oscillations are ubiquitous in the human brain and have been implicated in defined cognitive and behavioral states in precisely tuned neural networks. In neurodegenerative diseases, neurodegeneration is accompanied by changes in oscillatory activity, leading to the emerging concept of neurological and psychiatric disorders as "oscillopathies". Alzheimer's disease and Frontotemporal dementia, which represent the vast majority of age-related dementias, are characterized by significant alterations in brain oscillations. The restoration of oscillations through neuronal "entrainment" in animal models has shown a remarkable reduction in the neuropathological burden of toxic proteins, with a consequent significant increase in cognitive performance.

Transcranial alternating current stimulation (tACS) is a non-invasive neurophysiological technique for modulating the excitability of the central nervous system, which is gaining increasing therapeutic applications. Recent studies have demonstrated the effectiveness of this method in modulating natural brain oscillation frequencies underlying multiple cognitive processes such as verbal memory, perception, and working memory (Herrmann et al., 2013; Hoy et al., 2015).

A recent study conducted at our Center demonstrated the safety and clinical efficacy of tACS in Alzheimer's Disease, with significant improvement in memory and cholinergic circuits, which are primarily involved in the disease (see NP4479).

Based on these premises, we propose the same treatment with multiple home-based sessions in patients with mild Alzheimer's Disease to achieve a greater and more lasting effect over time. A brain stimulation system specifically designed for safe home use will be employed. The device is equipped with all safety controls to provide appropriate and safe stimulation. If inconsistencies (e.g., detached or mispositioned electrodes) or high impedances (e.g., improperly prepared electrodes) are detected, stimulation will automatically be interrupted. This procedure poses no greater risk to the patient at home than in a hospital setting and allows them to

[figure not shown][figure not shown][figure not shown]

CLINICA NEUROLOGICA - UNIVERSITA' DEGLI STUDI DI BRESCIA  
UO Neurologia 2 - AZIENDA SOCIO SANITARIA TERRITORIALE degli SPEDALI CIVILI DI BRESCIA  
Direttore: [name]

undergo treatment at home without the need for daily hospital visits over the four-month treatment period.

To evaluate the effects on brain transmission and the underlying mechanisms of this modulation, specific intracortical circuits will be investigated using transcranial magnetic stimulation (TMS), which depends on various neurotransmitters. Over the years, numerous TMS protocols have been developed to obtain neurophysiological parameter information for investigating both the pathogenesis and progression of certain neurodegenerative diseases. Cholinergic brain activity will be assessed using the short-latency afferent inhibition (SAI) protocol (Tokimura et al., 2000). Additionally, electroencephalographic modifications and biological parameters will be analyzed.

**OBJECTIVES:** The aim of this study is to evaluate clinical and biological response markers to home-based transcranial alternating current stimulation (tACS) supervised via telemedicine by investigators in patients with Alzheimer's disease (AD).

**PROCEDURES:** Patients followed at the Neurological Clinic, ASST Spedali Civili di Brescia, and the Neurology Unit, G. Giglio Institute Foundation, Cefalù (PA), with an AD diagnosis based on current clinical criteria, will be enrolled and randomized into two groups:

The first group (group 1) will undergo stimulation protocol using tACS (real), while the second group (group 2) will undergo placebo treatment (sham) (double-blind phase), with a real:placebo ratio of 1:1. Both group 1 and group 2 will then follow an open-label phase with real tACS stimulation. The treatment will be administered during the first week in the hospital, and thereafter, it will be provided at home with supervision from one of the experimenters via telemedicine.

During the first week, the patient and caregiver will receive training at the hospital, where staff will explain how to position and use the device. On the first day, staff will show the patient and caregiver the procedures. On the following days, they will let the caregiver manage the device and will provide support during treatment administration in order to enable the caregiver to manage the device independently at home. During this period, the study's medical staff will assess compliance with the correct procedures and, therefore, the caregiver's ability to manage the device independently. At the end of the training procedure, the investigator will assess the

[figure not shown][figure not shown][figure not shown]

CLINICA NEUROLOGICA - UNIVERSITA' DEGLI STUDI DI BRESCIA  
UO Neurologia 2 - AZIENDA SOCIO SANITARIA TERRITORIALE degli SPEDALI CIVILI DI BRESCIA  
Direttore: [name]

caregiver's ability to perform all stimulation procedures completely independently. If the caregiver is not completely independent, an additional week of training will be provided. If the caregiver is not completely independent in performing all necessary procedures independently at the end of the second week of training, the patient will be excluded from the study.

The device is easy to use, and switching it on and off, as well as the parameters, can be monitored remotely. The caregiver and patient cannot alter the set parameters, and due to the device's characteristics, they can only use the application at pre-set times and for a pre-set number of sessions, which are always set and monitored by the operator. During treatment (both sham and real), the device generates a code (reliability code) that allows the operator to know whether the procedure performed at home has been carried out correctly. If the device detects any anomalies (e.g., electrodes not positioned correctly, impedance too high), it locks itself and does not start treatment. The codes are automatically recorded by the device and can be read during the session and communicated by the patient to the operator by telephone. During the first week of home treatment, the caregiver will be asked to communicate the codes generated by the device to the center in order to verify that the procedures have been performed correctly. If the device is found to be incorrectly positioned > 50%, the caregiver will undergo further training at the center. Caregiver training at the center will be repeated a maximum of two times.

During the first week of home treatment, the patient will also be contacted ten minutes before each session by the center operator for support in managing the device. Patients and caregivers will be able to contact the investigator by telephone if necessary.

The patient will be given a copy of the device user manual (excerpt from the Italian version).

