#### **INCLUSION CRITERIA for patients:**

- Patients with mild Alzheimer's dementia (independent in basic and instrumental activities of daily living) according to current clinical criteria
- Signed Informed Consent Form
- Age  $\geq 18$  years
- Presence of a caregiver who can assist the patient and has successfully completed the necessary training for device use

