#### **INCLUSION CRITERIA for the caregiver:**

- Signed Informed Consent Form
- Age  $> 18$  years
- Compliance in participating in training on device usage
- Mini-Mental State Examination (MMSE)  $> 27/30$

[figure not shown][figure not shown][figure not shown]

CLINICA NEUROLOGICA - UNIVERSITA' DEGLI STUDI DI BRESCIA  
UO Neurologia 2 - AZIENDA SOCIO SANITARIA TERRITORIALE degli SPEDALI CIVILI DI BRESCIA  
Direttore: [name]

213

214 **EARLY WITHDRAWAL CRITERIA from the study:**

- 215 - Difficulty in managing the device, measured by the procedure failure rate, as  
216 indicated by the reliability code generated by the device after two training  
217 sessions at the center.

218

219 **STUDY DESIGN:** it is a monocentric, interventional, non-pharmacological,  
220 placebo-controlled, randomized, double-blind clinical study, as neither the patients  
221 nor those administering the evaluation tests will be aware of the type of treatment  
222 provided, real tACS or placebo, followed by an open-label phase. The stimulation  
223 equipment will be pre-programmed (real stimulation or placebo) by another operator  
224 who will not administer the stimulation itself or the tests, thus ensuring the  
225 experimental double-blind. Both the operator administering the treatment and the  
226 operator performing the evaluations will be unaware of the type of stimulation  
227 administered.

228 At baseline (T0), at the end of the double-blind phase (T1, 8 weeks), at the end of the  
229 open-label phase (T2, 16 weeks), and after further follow-up (T3, 24 weeks), each  
230 subject will undergo clinical and neuropsychological evaluation, TMS, EEG, and  
231 blood sampling for the assessment of biological markers such as NfL, pTau,  
232 Abeta40/42, and GFAP. The biological samples will then be sent to the Molecular  
233 Markers Laboratory at the IRCCS Istituto Centro San Giovanni di Dio  
234 Fatebenefratelli in Brescia for analysis of biological markers on extracellular vesicles  
235 from plasma or serum.

236 A subgroup of patients will undergo brain MRI (resting state) at baseline (T0) and at  
237 the end of the double-blind phase (T1, 8 weeks).

238 Each subject will then undergo two further follow-up visits with clinical evaluation at  
239 36 weeks (T4) and 72 weeks (T5) from T0.

240

241 **OBJECTIVES:**

- 242 - Primary objectives: evaluate the tolerability and safety of transcranial alternating  

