## END POINTS:

- Primary objectives: it is expected that tACS will be well tolerated (% of compliance >50%) and safe (absence of major adverse events) in the studied population. The effectiveness of the treatment will be evaluated on dedicated tests.

- Secondary objectives: the effectiveness of the treatment on imaging parameters will be evaluated. The effectiveness of the treatment on neurophysiological parameters and plasma neurodegeneration/amyloidosis will be evaluated.

- Exploratory objectives: it is expected that certain biological factors at baseline (e.g., ApoE genotype) may modulate the degree of response to tACS and thus predict the degree of clinical response.

**STATISTICAL PLAN:** as an experimental design, we will use a linear mixed-effects model (LME) with TIME (T0, T1, T2, T3) as a within-subject factor and TREATMENT (sham/real vs real/real) as between-subject factors, considering the subject modeled as a random intercept effect.

We performed a power analysis with G\*Power to estimate the sample size, based on some previously published studies (Benussi et al., *Brain Stimul* 2021; Dhaynaut et al., *J Alzheimers Dis* 2022; Zhou et al., *J Neurol Neurosurg Psychiatry* 2021), using methodologies similar to those applied in the study in question. The effect size  $f(V)$  was calculated using the direct method. Taking into account from the aforementioned studies an effect size equal to a partial  $\eta^2$  of 0.080, corresponding to an effect size  $f(V)$  of 0.295, and considering  $\alpha = 0.05$  and power  $(1-\beta) = 0.90$ , the expected sample size is 34 total subjects. Taking into account a possible attrition rate of 50%, appropriate for long-term studies in patients with Alzheimer's disease, who may have poor tolerability to the device, the final required sample size amounts to 50 total subjects (25 per group).

Correlation analyses (Pearson correlations corrected for multiple comparisons with False Discovery Rate) will be used to evaluate the correlations between biological parameters (plasma neurodegeneration markers) and clinical response. For dichotomous measures (ApoE and BDNF genotype), Fisher's exact test will be used.

**ETHICAL CONSIDERATIONS (RISK-BENEFIT):** tACS is a non-invasive, low-cost, and easy-to-implement technique that is gaining increasing popularity and an expanding range of potential therapeutic applications.

[figure not shown][figure not shown][figure not shown]

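### Failed caregiver training or device handling removes patients from the study after randomisation, which conflicts with the inclusion criterion and lets both primary comparisons rest on a selected group

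*Protocol*

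**What the plan says.** The Protocol fixes four things that bear on this point.

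- **Eligibility.** INCLUSION CRITERIA for patients asks for a caregiver who "has successfully completed the necessary training for device use". The criterion is in the past tense, as a condition of entry.
- **Order of events.** Under PROCEDURES, patients "will be enrolled and randomized into two groups", and "The treatment will be administered during the first week in the hospital, and thereafter, it will be provided at home". The training falls in the same period: "During the first week, the patient and caregiver will receive training at the hospital". The caregiver practises while treatment sessions are being given.
- **Removal.** A caregiver who is not independent after the first week gets a second week of training. If that fails, then "at the end of the second week of training, the patient will be excluded from the study". The list headed EARLY WITHDRAWAL CRITERIA from the study has one entry: "Difficulty in managing the device, measured by the procedure failure rate, as" shown by the device's reliability code after two training sessions at the centre.
- **Endpoint and assessments.** END POINTS gives the tolerability target: "it is expected that tACS will be well tolerated (% of compliance >50" percent). No denominator is stated. STUDY DESIGN sets assessments at T0, T1 (8 weeks), T2 (16 weeks) and T3 (24 weeks), and STATISTICAL PLAN models T0 to T3 with a random intercept per subject.

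**The concern.** An entry criterion cannot depend on something that happens only after the patient has been randomised and has begun allocated treatment. As written, sites must either enrol patients who do not yet meet the criterion or train caregivers at a time the Protocol does not describe.

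The larger problem is what follows from failure. Both rules take the patient out of the study, not merely off stimulation, and nothing in the Protocol keeps such a patient in follow-up. Two primary objectives are exposed. The efficacy comparison loses the outcomes of patients selected after randomisation. The tolerability result can be taken from people who handled the device successfully, although failing to deliver sessions correctly is closely related to what compliance measures.

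**Working it through.** **Timing.** STUDY DESIGN has the device pre-programmed as real or sham before it is used, and PROCEDURES runs the training during treatment sessions. Allocation therefore precedes training. This is an inference from the text, but a firm one, because no run-in or training step before randomisation is described.

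**Data left after removal.** A patient excluded at the end of the second training week leaves about six weeks before T1 and has a T0 record only. In a random-intercept model, a single baseline value helps estimate the baseline mean and the variance but says almost nothing about the difference between arms in change over time. Calling the analysis all-randomised would not recover data that were never collected. The early withdrawal rule is not dated. Where it acts before T1 the same holds.

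**Effect on compliance.** The plan has no figure of its own to reproduce here, because it gives no removal rate for these rules. Inputs:

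- Share of randomised patients removed, x: not in the documents. Assumed 10%, 20% and 30%.
- Scheduled double-blind sessions: 8 weeks × 5 days = 40.
- Sessions before exclusion in training: at most 2 weeks × 5 days = 10, which is 10/40 = 25%.
- Compliance read as the mean share of scheduled sessions delivered, with c the mean among patients kept. The Protocol does not say which reading it intends.

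With removed patients counted as zero, all-randomised compliance is (1 − x)·c. It exceeds 50% only if c > 0.50/(1 − x).

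With removed patients credited with 10 of 40 sessions, it is (1 − x)·c + 0.25x. It exceeds 50% only if c > (0.50 − 0.25x)/(1 − x).

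| x | Kept, of 50 | c needed, removed = 0 | c needed, 10 of 40 credited |
|---|---|---|---|
| 10% | 45 | 0.50/0.90 = 55.6% | 0.475/0.90 = 52.8% |
| 20% | 40 | 0.50/0.80 = 62.5% | 0.450/0.80 = 56.3% |
| 30% | 35 | 0.50/0.70 = 71.4% | 0.425/0.70 = 60.7% |

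Any c above 50% but not above the tabled value passes among patients kept and fails among all randomised. For example, with x = 30% and c = 60%, the all-randomised figure is 0.70 × 0.60 = 42% with no credit, and 0.42 + 0.075 = 49.5% with credit.

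**The case against.** **The denominator and analysis set belong in a statistical analysis plan.** This is fair, and their absence is not the finding. The Protocol permits a compliance figure based on successes only; it does not prescribe one. But a SAP cannot change the order of training and randomisation, and it cannot supply T1 data for patients who have left the study.

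**The rules test the caregiver, not the patient's tolerance.** This stands in part. Inability to operate the device differs from intolerance of stimulation, so the removed patients cannot simply be called tolerability failures. The overlap is with compliance, which is how the Protocol chose to define tolerability.

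**The sample size already allows for loss.** STATISTICAL PLAN assumes 50% attrition and moves from 34 to 50 subjects. Extra patients can restore precision but do not undo selection after randomisation. Nor is the margin wide: removal of 30% leaves 50 × 0.70 = 35, one above the required 34, before any other loss. A reader might apply the whole 50% allowance to these rules, but the Protocol does not attribute it to them and the result would be unstable. With 90% compliance among those kept, the all-randomised figure is 0.50 × 0.90 = 45% with no credit and 0.45 + 0.50 × 0.25 = 57.5% with credit.

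**Removal might differ by arm.** Sham current stops after 60 seconds, so a reader might infer that later faults, and hence withdrawals, arise only under real stimulation. The documents do not support this. Set-up is the same in both arms, the reliability code is generated in both, the operators are blinded, and the first rule turns on caregiver independence. No passage says that checks cease when sham current stops, or that an interruption counts towards withdrawal.

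**Conclusion.** The contradiction between the inclusion criterion and PROCEDURES is in the text and must be reconciled. As written, patients removed during training contribute T0 only, so efficacy is compared in a group selected after randomisation. The compliance target may also be judged on patients who handled the device successfully. Under assumed removal of 10% to 30%, compliance among those kept must exceed 55.6% to 71.4% (removed counted as zero) or 52.8% to 60.7% (10 of 40 sessions credited) for the all-randomised figure to pass 50%. These ranges rest on the assumed removal rates and on reading compliance as a mean share of sessions. Patients removed later than week 2 could have more sessions to credit, which would narrow the gap.

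A reader might go on to infer a bias in favour of real stimulation and try to put a size on it. The documents do not support that. Unequal removal is not shown, and a stable difference in level between removed and kept patients would largely cancel when change from T0 is compared. With equal removal in both arms, what is lost is the all-randomised comparison, some generalisability and sample size.

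**What to change.** Reconcile PROCEDURES and EARLY WITHDRAWAL CRITERIA with INCLUSION CRITERIA for patients:

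1. Complete caregiver training and the investigator's competence check before randomisation, and randomise only pairs who have passed. The inclusion criterion can then be met as worded.
2. For a handling failure after randomisation, separate stopping stimulation from leaving the study. The patient stays in the scheduled assessments, subject to consent, and is analysed in the assigned arm.
3. State that every randomised patient counts in the compliance denominator, and how undelivered sessions are scored.

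No stimulation rule needs to change.

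The cost is a protocol amendment, practice sessions that are not part of allocated treatment, and some off-treatment visits. Those visits are not trivial: T1 to T3 include neuropsychological testing, TMS, EEG and blood sampling. The compliance figure may also look less favourable.

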#### TREATMENT GROUP - GROUP 1:

The treatment group will undergo tACS sessions (real at 3 mA) applied at the cortical level for 60 minutes/day for 8 weeks, 5 days a week (Monday to Friday). The effects of tACS will be assessed both before and after stimulation, specifically evaluating cognitive performance using dedicated tests (i.e., CDR-SB, ADAS-Cog13, FNAT, ADCS-ADL), neurophysiological parameters (SAI using TMS and brain rhythms using electroencephalography [EEG]), and biological parameters (NfL, pTau, Abeta40/42, and GFAP). In a subgroup, effects on brain magnetic resonance imaging (resting state) will also be evaluated. A 6cc blood sample will also be taken to

[figure not shown][figure not shown][figure not shown]

CLINICA NEUROLOGICA - UNIVERSITA' DEGLI STUDI DI BRESCIA

UO Neurologia 2 - AZIENDA SOCIO SANITARIA TERRITORIALE degli SPEDALI CIVILI DI BRESCIA

Direttore: [name]

determine the ApoE and BDNF genotype, subject to the signing of an informed consent form, in order to evaluate any markers of clinical response.

#### PLACEBO GROUP - GROUP 2:

In the placebo group, the setup will be the same as for real stimulation; however, the electrical current will be automatically interrupted 60 seconds after the start of each stimulation, so that the placebo stimulation is indistinguishable from the real one. The same tests and assessments used during real stimulation will be applied.

After two months of treatment, all patients will undergo an open-label phase with real tACS for an additional 2 months, following the same protocol as group 1, and a subsequent follow-up 2 months after the end of treatment. In addition, two further follow-up visits will be carried out at three months and 12 months, where only clinical evaluation will be performed.

Analysis of Biological and Genetic Markers: the following biological and genetic biomarkers of response to tACS will be analyzed:

-ApoE and BDNF Genotyping: Genomic DNA will be extracted from whole peripheral blood using the Maxwell® 16 Blood DNA Purification Kit with the Maxwell® 16 Instrument (both Promega). The regions containing both APOE polymorphisms rs429358 and rs7412, as well as BDNF rs6265, will be amplified through polymerase chain reaction (PCR) using GoTaq® Hot Start Polymerase (Promega) or Optimase® Polymerase (ADS Biotech). PCR products will be purified with 0.5 mL Amicon® Ultra centrifugal filters (Merck Millipore). Sequencing will be performed using the AB Prism Big Dye Terminator Sequencing 3.1 kit (Life Technologies), following the manufacturer's instructions. The sequences will then be purified using ID MicroSEQ™ sequencing cleanup cartridges (Life Technologies) and loaded onto a 3500 Genetic Analyzer (Life Technologies). All sequences will be analyzed using Chromas software (Technelysium Pty Ltd).

- Plasma Marker Quantification (NfL, pTau, Abeta40/42, and GFAP): plasma NfL will be measured using the commercial NF-light® assay (Quanterix, Lexington, MA) according to the manufacturer's instructions. p-Tau, Abeta40/42, and GFAP will be measured using the Simoa platform.

-Analysis of extracellular vesicles (EVs) from blood with analysis of neurodegeneration/inflammation markers (miRNomic profile). EVs will be isolated from plasma/serum using a commercial kit (Total Exosomes Isolation Kit,

[figure not shown][figure not shown][figure not shown]

CLINICA NEUROLOGICA - UNIVERSITA' DEGLI STUDI DI BRESCIA  
UO Neurologia 2 - AZIENDA SOCIO SANITARIA TERRITORIALE degli SPEDALI CIVILI DI BRESCIA  
Direttore: [name]

Invitrogen) and analyzed using nanoparticle tracking analysis (NTA) on the NanoSight NS300 instrument (Malvern) to determine their concentration and size. miRNA expression analysis will be performed on EVs isolated from plasma/serum: small RNAs contained in circulating EVs will be extracted using commercial kits (e.g., exoRNeasy kit, Qiagen), libraries will be produced using commercial kits (e.g., QIAseq miRNA Library Kit Qiagen), and sequencing will be performed on the Illumina NextSeq2000 instrument.

